## Abstract

**Background:**

Preeclampsia (PE) is one of the most common hypertensive diseases, affecting 2%-8% of all pregnancies. The high maternal and fetal mortality rates of PE are due to a lack of early identification of affected pregnant women that would have led to closer monitoring and care. Recent data suggest that misfolded proteins might be a promising biomarker for PE prediction, which can be detected in urine samples of pregnant women according to their congophilia (aggregated) characteristic.

**Objective:**

The main purpose of this trial is to evaluate the value of the urine congophilia-based detection of misfolded proteins for the imminent prediction of PE in women presenting with suspected PE. The secondary objectives are to demonstrate that the presence of urine misfolded proteins correlates with PE-related maternal or neonatal adverse outcomes, and to establish an accurate PE prediction model by combining misfolded proteins with multiple indicators.

**Methods:**

At least 300 pregnant women with clinical suspicion of PE will be enrolled in this prospective cohort study. Participants should meet the following inclusion criteria in addition to a suspicion of PE: ≥18 years old, gestational week between 20+0 and 33+6, and single pregnancy. Consecutive urine samples will be collected, blinded, and tested for misfolded proteins and other PE-related biomarkers at enrollment and at 4 follow-up visits. Clinical assessments of PE status and related complications for all participants will be performed at regular intervals using strict diagnostic criteria. Investigators and participants will remain blinded to the results. Follow-up will be performed until 42 days postpartum. Data from medical records, including maternal and fetal outcomes, will be collected. The performance of urine misfolded proteins alone and combined with other biomarkers or clinical variables for the prediction of PE will be statistically analyzed.

**Results:**

Enrollment started in July 2023 and was still open upon manuscript submission. As of March 2024, a total of 251 eligible women have been enrolled in the study and enrollment is expected to continue until August 2024. Results analysis is scheduled to start after all participants reach the follow-up endpoint and complete clinical data are collected.

**Conclusions:**

Upon completion of the study, we expect to derive an accurate PE prediction model, which will allow for proactive management of pregnant women with clinical suspicion of PE and possibly reduce the associated adverse pregnancy outcomes. The additional prognostic value of misfolded proteins is also expected to be confirmed.

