### Recruitment

Potential participants will be identified by the research team from the antenatal clinic at Women’s Hospital, School of Medicine, Zhejiang University. Eligible women must meet all inclusion criteria without violating any of the exclusion criteria (Textbox 1) and will be provided with the participant information and consent form to sign. A research team member will provide a verbal explanation of the trial, including a description of the trial processes, the voluntary nature of the trial, and that a decision of whether or not to participate will not affect normal clinical care. No trial-related procedures will be performed on any individual without their prior written informed consent. All participants will be followed up until 42 days postpartum.

Inclusion and exclusion criteria for determining trial eligibility.Inclusion criteriaAged ≥18 years.Gestational week 20+0 to 33+6.Signed written informed consent.Single pregnancy.Clinically suspected preeclampsia (PE), meeting one or more of the following criteria:(i) new onset of elevated blood pressure (systolic ≥130 mmHg and/or diastolic ≥80 mmHg);(ii) aggravation of preexisting hypertension (increase of more than 30 mmHg systolic/15 mmHg diastolic from the basic blood pressure in patients without hypertension, or a significant increasing trend or increase beyond the controlled level based on the original treatment for patients with hypertension);(iii) new onset of proteinuria (no urinary tract infection);(iv) one or more clinical symptoms indicate suspected PE (other possible causes have been ruled out): upper abdominal pain, headache with impaired vision, fetal growth restriction, thrombocytopenia (platelets count<100×10^9^/L), liver function impairment (elevated blood concentrations of liver transaminases up to twice the normal concentration), and renal impairment (serum creatinine>1.1 mg/dL or a doubling of the serum creatinine concentration in the absence of other renal disease).Exclusion criteriaConfirmed diagnosis of PE/chronic hypertension with PE (superimposed PE).Confirmed diagnosis of eclampsia.Confirmed diagnosis of hemolysis with a microangiopathic blood smear, elevated liver enzymes, and low platelets (HELLP syndrome).Fetal chromosomal abnormalities.Concomitant participation in another clinical study.Received investigational intervention drugs in the past 3 months.Visible hematuria.Preexisting renal disease.

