### Study Groups: Classification of Cases and Controls

Standard diagnostic criteria [24,25] for PE are new onset of hypertension (systolic blood pressure≥140 mmHg or diastolic blood pressure≥90 mmHg measured on two occasions at least 4 hours apart) and new-onset proteinuria (≥300 mg/day or protein/creatinine ratio ≥0.3 mg/dL) after 20 weeks of gestation. Diagnostic criteria in the absence of proteinuria include any of the following: (1) thrombocytopenia (platelets count<100×10^9^/L); (2) liver function impairment (elevated blood concentrations of liver transaminases to twice the normal concentration); (3) renal insufficiency (serum creatinine>1.1 mg/dL or a doubling of the serum creatinine concentration in the absence of other renal disease); (4) pulmonary edema; and (5) central nervous system abnormalities or visual disturbances.

Cases are defined as patients who develop PE at any time between the first visit to 6 weeks (42 days) postpartum.

Controls are patients who do not develop PE throughout the pregnancy and up to 6 weeks (42 days) postpartum.

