### Selection of Predictor Variables

According to the objective of this study, the misfolded protein level in urine will be considered as a predictor candidate for PE onset or adverse outcomes. Other preset variables include: (1) demographic factors, including high-risk factors of PE; (2) urine biomarkers reported in the literature; (3) medication; and (4) routine clinical variables or laboratory tests in daily practice (Textbox 2). The determination of valid variables will be based on the statistical analysis results with a significance level of *P*<.05.

Preset variable candidates for model development.Demographic factorsAgeBMIConception modeParityPreexisting hypertension, diabetes, autoimmune diseases (systemic lupus erythematosus, antiphospholipid syndrome)Urine biomarkersMisfolded proteinsPlacental growth factorSoluble FMS-like tyrosine kinase 1Total proteinCreatinineMedicationAspirinAntihypertensive drugsRoutine clinical variables or laboratory testsBlood pressureAspartate aminotransferaseLactate dehydrogenaseSerum creatinineProteinuria (spot urine protein, 24-hour urine protein)Uterine artery pulse index

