## Discussion

### Study Implications

Many potential PE biomarkers have been identified using samples from patients with a confirmed diagnosis of PE in comparison with samples obtained from normal pregnancies, which represents a convenient and pragmatic approach for biomarker identification. Although these studies have generated excellent candidate biomarkers for PE detection, there has been less focus on biomarkers that can be used in PE risk prediction. It is possible that biomarkers that are differentially expressed in patients with PE versus those without will fail in a predictive verification study. Thus, a prospective cohort with an uncertain subsequent PE status would provide the best avenue for exploring PE prediction models. To our best knowledge, this is the first prospective study to explore the predictive value of a congophilia-based detection tool in pregnant women with a clinical suspicion of PE in China. The study will be conducted in a high-quality tertiary hospital focused on women’s health. Maternal age of 35 years or older; nulliparity; and preexisting hypertension, diabetes, and autoimmune diseases (eg, systemic lupus erythematosus and antiphospholipid syndrome) are the main high-risk factors for PE [25] and will be included as predictive variables in our analysis. High-risk pregnant women are recommended to use low-dose aspirin to prevent PE; therefore, it is appropriate to consider medication with aspirin as a variable candidate. The crucial biomarkers of PE [22,23], such as PlGF, sFLT-1, and routine clinical variables or laboratory tests, are also under evaluation to build a prediction model. Another important feature of this study is the use of blinding, which ensures that the participants’ laboratory data have no influence on the diagnosis of PE as well as the clinical decisions of treatment.

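### P<.05 variable selection cannot show what the urine test adds to Visit 1 findings that, in some women, are already part of the PE definition

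*Protocol article*

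**What the plan says.** **Entry (Recruitment, Textbox 1).** Suspected PE means "meeting one or more of the following criteria". The list includes "new onset of elevated blood pressure (systolic ≥130 mmHg and/or diastolic ≥80 mmHg"), "new onset of proteinuria (no urinary tract infection"), and a group of clinical findings that includes low platelets, liver impairment and renal impairment.

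**Outcome (Study Groups).** PE is hypertension from 140/90 mmHg together with "new-onset proteinuria (≥300 mg/day or protein/creatinine ratio ≥0.3 mg/dL) after 20 weeks of gestation". Without proteinuria, the second component can be low platelets, liver impairment, renal insufficiency, pulmonary edema, or central nervous system or visual disturbance.

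**Bars (Sample Size).** Target NPV is 99% and target PPV 54%, with 15% testing positive. A sample of 280 is said to be sufficient to detect NPV above 90% and PPV above 25% with 80% power at a Type I error of .05. Entry findings play no part in these criteria.

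**Model (Selection of Predictor Variables; Statistical Analysis).** Textbox 2 lists misfolded proteins with urine total protein, urine creatinine, proteinuria, blood pressure and others. "The determination of valid variables will be based on the statistical analysis results", at P<.05. The method is logistic regression, univariable or multivariable.

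**Conclusion expected (Abstract, Conclusions).** "The additional prognostic value of misfolded proteins is also expected to be confirmed".

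**Blinding (Discussion, Study Implications).** Blinding is said to ensure that participants' "laboratory data have no influence on the diagnosis of PE".

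**The concern.** A woman who enters with new-onset proteinuria or a qualifying organ finding needs only hypertension to become a case. Proteinuria at entry is therefore likely to predict the outcome partly by definition. The index test also reads protein in urine. If its result largely tracks entry proteinuria, its unadjusted NPV, PPV and P value will look good without telling the clinician anything new.

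Selection at P<.05 does not settle this. With overlapping candidates and few cases, it can keep the misfolded protein result and drop proteinuria, or the reverse. Neither outcome measures what the test adds to blood pressure and urine protein at Visit 1. A redundant test could be credited with added value. A useful one could be discarded because predictors that belong to the diagnosis have a built-in advantage.

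**Working it through.** **1. Overlap, side by side.** New-onset proteinuria, platelets below 100×10^9/L, liver impairment and raised creatinine appear in both the entry list and the PE definition. Blood pressure of 130-139/80-89 mmHg, upper abdominal pain and fetal growth restriction allow entry but are not diagnostic components. The overlap therefore applies to some entrants, not all.

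**2. The plan's own sample size.** Expected positives are 0.15×280 = 42 and negatives 238.
- Exact two-sided .05 test of PPV=25%: 17 or more true positives of 42 are needed (upper tail 0.0197; 16 would give 0.0416, above .025). Power at 54% is 97%.
- Exact test of NPV=90%: 224 or more PE-free of 238 are needed (upper tail 0.0170). Power at 99% is above 99.9%.
- Joint power with a random number of positives is 96%. So 280 is sufficient, though more than 80% power requires. For PPV, the two-sided score formula gives ((1.96×√(0.25×0.75) + 0.842×√(0.54×0.46))/0.29)² = 19.1, so 20 positives, or 20/0.15 = 134 women.
- Dropout: 280/0.94 = 298, consistent with 300.
- Implied PE rate: 0.15×0.54 + 0.85×0.01 = 8.95%, or about 25 cases in 280. With no test, 91% would be PE-free, so an NPV bar of 90% filters little and the PPV bar does most of the work.

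**3. A test that only flags entry proteinuria (assumed rates).** Let a share q of women enter with proteinuria and test positive, with PE risk r1, and let all others test negative, with risk r0. The chance of passing both bars is the sum over k of P(k positives | 280, q) × P(PPV bar passed | k, r1) × P(NPV bar passed | 280−k, r0).

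| r1 / r0 | q=10% | q=15% | q=20% | q=30% |
|---|---|---|---|---|
| 54% / 1% | 85% | 96% | 99% | >99% |
| 45% / 3% | 55% | 74% | 85% | 94% |
| 40% / 4% | 33% | 47% | 59% | 73% |
| 35% / 5% | 14% | 20% | 26% | 34% |

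The first row at q=15% equals the plan's joint power because it gives the proteinuria flag the plan's own target values.

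**4. Does adjustment change the answer?** In 1,000 simulated trials per setting (q=15%, risks 54%/1% and 45%/3%), the test disagreed with proteinuria in 2% or 5% of women and carried no information of its own. The unadjusted comparison gave P<.05 in every run. The likelihood-ratio test of the test term, with proteinuria in the model, gave P<.05 in about 3% to 6% of runs. With complete agreement the adjusted effect cannot be estimated. Whether proteinuria is in the model therefore decides the conclusion, and the stated rule leaves that to the data.

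**5. Blinding.** Ethical Considerations and Urine Coding withhold the study's test results. The PE definition uses proteinuria, platelets, transaminases and serum creatinine. Laboratory data therefore do determine the diagnosis, and three of the candidates in Textbox 2 (proteinuria, aspartate aminotransferase, serum creatinine) relate directly to diagnostic criteria.

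**The case against.** **Joint modelling is planned.** A reader might infer that nothing in the plan separates the test from proteinuria. The text does not support that. The Abstract's Methods plan performance alone and in combination, Textbox 2 lists proteinuria and blood pressure beside the test, and multivariable regression is available. Step 4 shows that such a model would usually expose a proxy. What stands is that adjustment is optional and retention depends on P<.05.

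**Detail belongs in the SAP.** This is a condensed article, and forced covariates and nested comparisons are often specified elsewhere. That would answer a complaint about silence alone. Here, though, the article states a selection rule and announces a conclusion that the rule cannot carry.

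**The sentence may mean something else.** 'Additional' may point to the secondary objective on maternal and neonatal adverse outcomes rather than to value beyond proteinuria. This is a fair reading, so the point is conditional and the sentence needs clarifying.

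**The bars are not so easily passed.** A reader might infer that a proteinuria flag with 30% or 35% PE risk already succeeds, because 30% and 35% exceed 25%. With about 25 cases in total, NPV would be 1 − 12.46/238 = 94.8% or 1 − 10.36/238 = 95.6%. But 25% and 90% are values to be rejected by a test. True positives of 12.6 or 14.7 fall short of the 17 needed, and the chance of passing both bars is 6% and 23%. This objection stands in full; only higher risks make a pass likely.

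**Overlap is inherent.** Enrolling women with suspected PE is the purpose of the study. That is true, and it is why the added value must be isolated in the analysis.

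**Conclusion.** The point holds in a conditional form. Some entrants, not all, already have a component of the PE definition, and the index test is a urine protein assay. P<.05 selection in univariable or multivariable regression cannot support a claim of value beyond Visit 1 findings, if that is what the Abstract's sentence means.

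With 15% positive and 280 women, a pure proteinuria flag would pass both bars with probability from 20% (35%/5%) to 96% (54%/1%). This rests on assumed rates, on exact two-sided testing, and on the extreme case of a test identical to entry proteinuria. The documents give neither the share entering with proteinuria nor their PE risk, and they do not say how closely the test tracks proteinuria. The figures show what the bars cannot rule out, not what the test does.

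Separately, the Discussion's blinding sentence is wrong as written and should be narrowed.

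**What to change.** 1. Base any added-value conclusion on one prespecified nested comparison. The reference model holds Visit 1 blood pressure and Visit 1 urine protein/creatinine ratio whatever their P values. Then add the misfolded protein result and report the likelihood-ratio test and the change in AUC with its confidence interval.
2. Report NPV and PPV separately for women with and without proteinuria at entry, as a descriptive result.
3. State whether 'additional prognostic value' means value beyond Visit 1 findings or association with adverse outcomes.
4. Limit the blinding claim in Study Implications to the study's own urine assays: misfolded proteins, PlGF, sFLT-1 and the study-laboratory protein/creatinine ratio.

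Cost: wording and one extra analysis. Table 1 already schedules the data at Visit 1, and the article says analysis starts only after follow-up is complete. The downsides are two degrees of freedom spent with about 25 expected cases, imprecise subgroup estimates, and possibly a smaller reported value for the test.

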**Trial Registration:**

Chinese Clinical Trials Registry ChiCTR2300074878; https://www.chictr.org.cn/showproj.html?proj=202096

**International Registered Report Identifier (IRRID):**

PRR1-10.2196/54026

## Introduction

### Background

Preeclampsia (PE) is one of the most common hypertensive diseases in pregnancy, characterized by elevated blood pressure accompanied by proteinuria or organ damage after 20 weeks of gestation [1]. The incidence of PE is approximately 2%-8% worldwide [2,3], and each year, an estimated 76,000 women and 500,000 fetuses die from PE and related complications [4]. Symptoms of PE are not specific, including headache, visual impairment, upper abdominal pain, and shortness of breath, among others. In severe cases, PE may develop into eclampsia, which involves seizures or coma [5-7]. PE may also lead to placental abruption; intrauterine growth restriction; hemolysis with a microangiopathic blood smear, elevated liver enzymes, and low platelets (ie, HELLP syndrome, a life-threatening liver and blood clotting disorder); and other serious health consequences for both the pregnant woman and fetus [8,9]. To date, the treatment of PE has mainly involved the use of antihypertensive medications such as methyldopa, labetalol, and hydralazine to lower blood pressure and prevent further maternal complications [10-12], and magnesium sulfate is also administered to prevent seizures in severe cases [13]. However, the only curative treatment of PE is to deliver the placenta. The current clinical strategy for PE is focused on the early screening and close monitoring of high-risk pregnancies, since low-dose aspirin therapy has proven to be effective in reducing the risk of developing PE by 62% [14]. Although potential biomarkers and ultrasonic techniques for detecting PE have been evaluated in recent decades, none has adequate positive or negative predictive value for the prediction of PE [15-17]. 

With increasing knowledge of the condition, six stages of PE have been proposed [6]. Defective placentation (stage 3) results in oxidative stress, and placental-derived products are released into the maternal blood (stage 4) before PE is diagnosed (stage 5). Recently, an increased level of misfolded proteins in the urine has been identified in patients with PE [18], suggesting that PE might share pathophysiologic features with recognized protein misfolding disorders such as Alzheimer disease. In patients with PE, misfolded proteins such as amyloid beta and transthyretin can accumulate in the circulation to exert neurotoxic effects and activate inflammatory cascades, leading to endothelial dysfunction and oxidative stress. Buhimschi et al [18] demonstrated that a dot test using Congo Red, a synthetic diazo dye with specific affinity for misfolded proteins, to visualize this aggregation feature (ie, congophilia) for detecting the presence of misfolded proteins in urine could serve as a promising diagnostic tool for PE. Li et al [19] subsequently developed a simple and rapid point-of-care testing (POCT) tool to detect the presence of misfolded proteins in urine based on visual observation, which achieved an overall sensitivity of 73.6% that reached up to 83% for severe PE cases.

The traditional approach for PE screening is to identify risk factors based on maternal demographic characteristics and medical history; however, this approach can only identify 35% of total PE cases and 40% of preterm PE cases, with a false-positive rate of approximately 10% [20,21]. A noninvasive laboratory method involving measurement of the ratio of soluble FMS-like tyrosine kinase 1 (sFLT-1) to placental growth factor (PlGF) in the urine proved to be effective in PE diagnosis, achieving a sensitivity of 70%-72.5% with a 5%-14% false-positive rate [22,23]. Thus, combining urine PlGF and sFLT-1 testing with other biomarkers may yield the best predictive performance.

In this trial, we will test a new congophilia-based detection method alone or combined with clinical variables and other urine biomarkers to predict the onset of PE before its clinical manifestation. This work can therefore help clinicians better identify PE earlier, enabling the proactive management and monitoring of pregnant women who exhibit signs or symptoms of PE but do not meet the current diagnostic criteria.

### Objective

The primary objective of this study is to assess the short-term predictive potential of the new congophilia-based detection tool for PE onset in pregnant women with a clinical suspicion of PE. That is, we aim to confirm whether the urine misfolded protein level can be used to rule in or rule out PE in the short term. The secondary objectives are to evaluate whether the urine misfolded protein level correlates with PE-related maternal or neonatal adverse outcomes and to establish an accurate PE prediction model by combining misfolded protein values and multiple indicators.

## Methods

### Study Design

This is a prospective noninterventional clinical trial planned in accordance with the principles of evidence-based medicine using the PICO (patient, problem, or population; investigated condition; comparison; and outcome) criteria. The study procedure is outlined in Figure 1.

**Figure 1 figure1:**
[figure not shown]
Flowchart of participants with suspected preeclampsia (PE) in the trial. Eligible pregnant women will be enrolled, and consecutive urine samples will be collected at each visit. Urine samples will be blinded and tested for misfolded proteins and other PE-related biomarkers. No intervention according to the test results will be introduced. Required clinical information will be collected from patients’ medical records. crea: creatinine; PlGF: placental growth factor; sFLT-1: soluble FMS-like tyrosine kinase 1; TPUC: Total Protein in Urine.

